## Discussion

5.

ASD is a complex and heterogeneous disease with multiple phenotypes. Its underlying cause is unknown, and no curative drugs or treatments are currently available. However, increasing evidence from animal studies and clinical research supported a link between the microbe-gut-brain axis and ASD (Cryan et al., 2019; Martinez-Gonzalez and Andreo-Martinez, 2020). Gastrointestinal symptoms are a common complication in children with ASD, with affected children four times more likely to experience symptoms such as diarrhea, constipation, and abdominal pain than non-ASD children (Patusco and Ziegler, 2018). Some of these symptoms, such as reflux and vomiting, can disrupt the daily activities of children with ASD and are often accompanied by other symptoms, such as an imbalanced intestinal flora, increased intestinal permeability, inflammation, and food allergies (Buie et al., 2010).

Furthermore, there were evidences suggesting that FMT may be effective in improving both ASD behavior and gastrointestinal symptoms by improving intestinal microecology. Preclinical experiments have shown that FMT could improve autistic behavior, and fecal bacteria from wild mice have been found to improve autistic behavior, metabolic levels, memory, and social skills in ASD mice (Li et al., 2020). Kang et al. used FMT in combination with antibiotics, omeprazole and Movi Prep therapeutic drinks, which increased the abundance of Bifidobacterium, Prevotella, and Desulfovibrio, leading to improvements in ASD and gastrointestinal symptoms that lasted for at least 8 weeks (Kang et al., 2019) which also led to changes in serum and intestinal metabolites (Kang et al., 2020). Li et al. found that FMT improved gastrointestinal symptoms and ASD symptoms, promoted a shift in the intestinal flora of children with ASD to that of typical neurological children, and significantly altered serum levels of neurotransmitters (Li et al., 2021). Additionally, Zhao et al. found that FMT was statistically different in improving gastrointestinal symptoms and ASD symptoms, improved gut microbiology, and caused only mild, transient adverse events in 29.2% of patients (Zhao et al., 2019). These studies demonstrate that FMT is a safe and effective treatment that contains at least 1,000–1,150 functional bacteria (Zhang et al., 2012), making it an ideal treatment option for improving gut microecology and the effectiveness of treatment for ASD.

Although FMT has been shown to effectively improve the symptoms of ASD, there is still no consensus on the optimal dose and treatment regimen for FMT in ASD patients (De Angelis et al., 2015). Chen et al. used an individualized daily intake of fecal bacteria (Chen et al., 2022). Our study will use standard bacterial fluids administered in three phases: first-dose treatment, intensive treatment, and maintenance treatment. Prior to treatment, antibiotics were used to clean the bowel, making this the first study to use bacterial fluids in three phases of treatment, which has significant implications for the further development of clinical applications of FMT. The critical period after antibiotic use was likely the most favorable for colonizing the gut by foreign bacteria (Kang et al., 2019). Therefore, our study’s first week of treatment will involve a high bacterial dose, followed by three weeks of intensive treatment and eight weeks of maintenance treatment. The bacterial liquid in this study will be dissolved in drinks, making it easier for children with ASD to swallow, which will increase the acceptability of FMT treatment. This study hypothesizes that FMT will target specific ASD symptoms, gastrointestinal symptoms and sleep symptoms, and aim to identify the bacteria and metabolites associated with improved symptoms. This study is a double-blind randomized controlled trial, but some limitations still exist. Firstly, the sample size might be small, with only 42 patients enrolled in this study. Further expansion of sample size will need to demonstrate the efficacy of fecal microbiota transplantation fluid for autism. Secondly, future trials will group children with ASD according to different core symptoms to explore the precise targeting of FMT treatment for ASD symptoms and compare the effects of FMT treatment within and between groups. Thirdly, a longer follow-up time will enable better observation of the duration of improvement in ASD symptoms and the safety and efficacy of FMT. This study will have only one follow-up and willnot track the long-term impact of FMT on children with ASD. Fourthly, besides diet, probiotics and other factors, there are many factors affecting gut microbiota. This study will not fully consider the mixed factors affecting gut microbiota, such as living habits, age, etc.

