
Fecal microbiota transplantation (FMT) is a procedure that involves transferring fecal microorganisms from a healthy individual to a patient’s gastrointestinal tract, with the aim of improving the intestinal microecology and treating the disease (Liu et al., 2022). Studies have shown that FMT can improve symptoms of ASD, as well as gastrointestinal symptoms and intestinal microecology (Tan et al., 2021). The intestinal microecology is diverse and complex, and FMT contains around 1,000–1,150 functional bacteria that colonize the host gut more efficiently than prebiotics or probiotics (Vendrik et al., 2020). Although no serious adverse events have been identified in studies of FMT for ASD, clinical adverse effects such as fever and allergies have been observed in children with ASD treated with FMT (Zhao et al., 2019). Therefore, the efficacy and safety of FMT need to be further evaluated. More research is needed to understand how FMT improves ASD symptoms by altering intestinal flora and metabolites (Xu et al., 2021). Additionally, there is still no consensus on the optimal dose or duration of FMT for the treatment of ASD. This study is a double-blind randomized controlled trial with the primary aim of assessing the improvement of ASD symptoms with FMT. By analyzing the correlation between changes in the scale of autism-related symptoms and gut flora and metabolites in a reasonable grouping, sample size, dosing method and treatment phase, we sought to identify the unique bacterial and metabolic markers of ASD that may provide additional evidence for the “microbial-gut-brain axis” and the treatment of ASD symptoms with FMT. This study will have important implications for treating patients with ASD associated with gut microecological dysbiosis.

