### Study design

2.1.

This is a single-center, double-blind, double-modeled, randomized, interventional clinical study aiming at exploring the efficacy and safety of FMT formulation on an interventional treatment of children with ASD. The degree of improvement in their symptoms will be assessed using several scales. Additionally, changes in the composition and structure of their intestinal flora and metabolites of the flora in their blood, urine and feces before and after treatment will also be assessed by macro-genomic sequencing and metabolomics. The study will also evaluate the differences in the gut flora of children with ASD and healthy children and the acceptability of FMT pediatric preparations by children with ASD and their legal guardians.

The primary endpoint of the study is the change from baseline in Childhood Autism Rating Scale (CARS) scores in children with ASD after 12 and 24 weeks of treatment. The secondary endpoints are the variations in assessment scales, and gut flora and included five main points:

(1) Variations in scores from baseline in the Social Responsiveness Scale (SRS), Autism Behavior Checklist (ABC), Psychoeducational Profile Third Edition (PEP3), Gastrointestinal Symptom Rating Scale (GSRS), and Children’s Sleep Habits Questionnaire (CSHQ) after 12 and 24 weeks of treatment;(2) Variations in gut flora characteristics (including alpha-diversity, flora composition, beta-diversity, colonizing bacteria, differential bacteria, and metabolic pathway function) in children with ASD after treatment compared to baseline and donors;(3) Differences in intestinal flora characteristics (including alpha-diversity, flora composition, beta-diversity, differential bacteria, and metabolic pathway function) between children with ASD (baseline) and healthy children;(4) The incidence of adverse events during the treatment of children with ASD;(5) Variations in the FMT acceptance scale scores for participants with ASD and their legal guardians.

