The patients will be divided into two cohorts: Cohort 1 will include 42 children aged 3–9 years diagnosed with ASD, while Cohort 2 will include 30 healthy children aged 3–9 years. The sex ratio and age range of children enrolled in Cohort 1 and Cohort 2 will be kept roughly the same. In Cohort 1, subjects who meet the entry criteria will undergo a two-week screening visit after the legal guardian signs the informed consent. They will then be randomly allocated to either the trial or control group in a 2:1 ratio. Children in the trial group will undergo rehabilitation and FMT, while the control group will receive rehabilitation and placebo. All children will undergo a 12-week treatment period following the completion of bowel preparation and followed up for 12 weeks, during which they will receive only rehabilitation. A homogenous rehabilitation scheme will be performed on all the ASD children in Cohort 1. The study participants will be discharged at week 25 after the end visit. In Cohort 2, after the legal guardian signs the informed consent, they will undergo a physical examination, assessment of vital signs, and various laboratory examinations within two weeks to confirm their health status. Blood, urine, and fecal samples will be collected within one week, and the children will be discharged. Metabolomics analysis will be performed on blood and urine samples, while macro-genomic sequencing and metabolomics analysis will be conducted on fecal samples.

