### Inclusion/exclusion criteria

2.2.

The study participants in each cohort will meet all inclusion criteria to be eligible for this trial. For cohort 1, the patients will:

(1) have a diagnosis of autism as outlined by a child psychiatrist according to the Diagnostic and Statistical Manual of Mental Disorders (5th edition) and positive results on both the Autism Diagnostic Observation Schedule and Autism Diagnostic Interview-Revised assessments;(2) age 3–9 years, regardless of gender;(3) not have immunodeficiency disorders;(4) provide signed ICF by participants’ legal guardians who fully understand the study;(5) have an ABC score ≥ 62 at the time of screening;(6) meet two of the following scale scores at the time of screening: Childhood Autism Rating Scale (CARS) score ≥ 38; Social Responsiveness Scale (SRS) score ≥ 75.

For cohort 2, the patients will:

(1) age 3–9 years;(2) have a male to female ratio as close to cohort 1 as possible;(3) provide signed ICF by participants’ legal guardians who fully understand the study;(4) have normal physical examination, vital signs and important laboratory test results.

Subjects meeting any of the following exclusion criteria will not be allowed to participate.

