**Figure 2 fig2:**
[figure not shown]
Overall process of the clinical trial.

**Table 1 tab1:** Inspection schedule for cohort 1.

Parameters	Baseline	Bowel preparation	Treatment period						Follow-up
			First dose treatment	Intensive treatment	Maintenance treatment				
Time window	D-21 ~ D-7	D-6 ~ D-1	D1 ~ D7	D8 ~ D28	D29 ~ D42	D43 ~ D56	D57 ~ D71	D71 ~ D84	D85 ~ D169
Informed consent	X								
Inclusion and exclusion criteria	X								
Demographic data^a^	X								
Medical and treatment history	X								
Height	X								
Weight	X							X	X
Vital signs^b^	X							X	X
Allergy history	X								
Health checkup	X							X	X
Routine blood test	X							X	X
Blood biochemistry	X							X	X
Urinalysis	X							X	X
Fecal routine	X							X	X
Fecal sample collection^c^	X			X		X		X	X
Urine sample collection^c^	X			X		X		X	X
Blood sample collection^c^	X							X	X
Bowel preparation		X							
FMT			X						
CARS	X			X		X		X	X
SRS	X			X		X		X	X
GSRS	X			X		X		X	X
ABC	X			X		X		X	X
CSHQ	X			X		X		X	X
PEP3	X			X		X		X	X
rehabilitation training	X								
Acceptance survey^d^			X	X				X	
Diet Record	X								
Adverse event record	X								
Combined medication record	X								

FMT, Fecal Microbiota Transplantation; CARS, Childhood Autism Rating Scale; GSRS, Gastrointestinal Symptom Rating Scale; ABC, Autism Behavior Checklist; PEP3, Psychoeducational Profile(Third Edition); SRS, Social Responsiveness Scale; CSHQ, Children’s Sleep Habits Questionnaire.

1 Demographics: date of birth, age, sex, ethnicity.

2 Vital signs: temperature, blood pressure, heart rate (pulse), respiratory rate.

3 Sample collection:

a Stool sample collection: Stool samples will be collected for macro-genome sequencing and metabolomic analysis during the screening period, every fortnight after the start of treatment for macro-genome sequencing, and every four weeks for metabolomic analysis until the end of the study.

b Urine sample collection: Urine samples will be collected for metabolomic analysis during the screening period and every four weeks from the start of treatment until the end of the study.

c Blood sample collection: Blood samples will be collected for metabolomic analysis during the screening period, at the end of treatment (week 13), and at the end of the study (week 25) for metabolomic analysis and safety data collection in the blood.

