d Acceptance questionnaires: Part A and Part B questionnaires will be completed by legal guardians only during the screening period; Part A and Part B questionnaires will be received by subjects and/or legal guardian at the end of the first dose of treatment, booster treatment and maintenance treatment, respectively, (see appendix for details).

##### Cohort 2

2.5.2.2.

After the legal guardian signs the ICF, during the screening period (D-14 to D0), the patient’s demographic information (including date of birth, age, sex, and ethnicity), medical and treatment history, allergy history, vital signs (such as temperature, blood pressure, heart rate, and respiratory rate), physical examination, height and weight measurements, as well as data from routine blood, blood biochemistry, urine and fecal tests will be collected and evaluated to determine the patient’s health status.

After the legal guardian signs the ICF, the screening period (D-14 to D0) will involve collecting demographic data (such as birth date, age, gender, and nationality), important medical history, treatment history, and allergy history of the subjects. Vital signs, including temperature, blood pressure, heart rate, respiratory rate, physical examination, height and weight measurements, as well as data from routine blood, blood biochemistry, urine and fecal tests, will also be recorded to determine the patient’s health status.

During the sampling period (D1 to D7), one stool sample will be collected for macroeconomic and metabolomic analysis, and one urine sample and a blood sample will also be collected for metabolomic analysis (Table 2 and Figure 2), following which they will be eligible for discharge.

**Table 2 tab2:** Inspection schedule for Cohort 2.

Parameters	Baseline	Sample collection period
Time windows	D-14 to D0	D1 to D7
Informed consent	X	
Inclusion and exclusion criteria	X	
demographic data^1^	X	
Medical and treatment history	X	
Vital signs^2^	X	
allergy history	X	
health checkup	X	
routine blood test	X	
Blood biochemistry	X	
Urinalysis	X	
Fecal routine	X	
Fecal sample collection^3^		X
Urine sample collection^3^		X
Blood sample collection^3^		X

1 Demographics: date of birth, age, sex, ethnicity.

2 Vital signs: temperature, blood pressure, heart rate (pulse), respiratory rate.

3 Stool sample collection: Stool samples will be collected for macro-genome sequencing and metabolomic analysis during the screening period.

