### Statistical analysis

2.6.

Bioinformatics and statistical analyses will be conducted by professionals using specialized software tools. Analysis of clinical scale results will involve comparing changes in ABC, CARS, SRS, GSRS, CSHQ and PEP3 scales before and after FMT. Differences in scale results between pre- and post-treatment and control groups will also be assessed. To analyze gut flora and metabolites, we will examine alpha-diversity, beta-diversity, bacterial symbiotic networks, and metabolome analysis using the R language MetaboAnalystR package. This package will enable the quantification of metabolite content and the identification of characteristic metabolites. Mann–Whitney U and Kruskal-Wallis tests will be used to analyze differences in gut flora and metabolites between groups. To explore the correlation between gut flora, metabolites, and improvements in ASD symptoms, gastrointestinal symptoms, and sleep symptoms, we will use Spearman’s correlation test.

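### The baseline flora comparison of ASD with healthy children is not randomised and only roughly matched on age and sex, and the only tests named for it cannot adjust for either

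*Protocol article*

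**What the plan says.** Section 2.1 (Study design) lists as secondary endpoint 3: "Differences in intestinal flora characteristics (including alpha-diversity, flora composition, beta-diversity, differential bacteria, and metabolic pathway function) between children with ASD (baseline) and healthy children". This serves secondary aim 2 in the Introduction. The last sentence of the abstract extends the comparison with healthy children to metabolism, and Cohort 2 gives blood, urine and stool for that purpose.

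On making the cohorts comparable, the abstract says the healthy children will resemble the ASD children in age and gender. Section 2.1 gives the means: "The sex ratio and age range of children enrolled in Cohort 1 and Cohort 2 will be kept roughly the same". Among the Cohort 2 criteria in section 2.2, the one on sex is "have a male to female ratio as close to cohort 1 as possible"; the one on age is only the span of 3–9 years.

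On analysis, section 2.6 says: "Mann–Whitney U and Kruskal-Wallis tests will be used to analyze differences in gut flora and metabolites between groups". It describes no adjusted, stratified or matched analysis. The Discussion lists among the limitations: "This study will not fully consider the mixed factors affecting gut microbiota, such as living habits, age, etc".

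The footnotes to both inspection schedules (Tables 1 and 2) record the same items: "Demographics: date of birth, age, sex, ethnicity". Age and sex are therefore available for every child in both cohorts.

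**The concern.** Randomisation in this trial separates FMT from placebo within Cohort 1. It does nothing to balance children with ASD against healthy children, so that contrast depends on how Cohort 2 is recruited and on the analysis. An equal age range does not give an equal age distribution: one cohort could lie mostly near 3–5 years and the other near 7–9, and both would meet the criteria. The article itself names age as a factor that affects the flora. A rank test of ASD against healthy children would then attribute part of an age difference to ASD. At stake is whether the taxa and metabolites reported under secondary endpoint 3, and under the parallel metabolite comparison, reflect ASD or age.

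**Working it through.** **Plan's own figure.** There is none to reproduce. Section 2.3 calls 30 healthy children sufficient without an effect size, SD, alpha or power.

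**Inputs from the documents.** 42 children with ASD, 30 healthy children, ages 3–9 years in both cohorts, and the Mann–Whitney U test.

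**Inputs assumed.** Two-sided 5% level; ages spread over 3–9 years, uniform when there is no gap; a difference in population mean age of 0 to 1 year; an age–feature correlation r of 0.2 to 0.5; no true ASD effect. The documents give none of these.

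**Step 1: the shift that age alone produces.** The SD of a uniform age on 3–9 years is 6/√12 = 1.732 years. A mean age gap g moves a standardised feature by r × g / 1.732. The standard error of a standardised group difference is √(1/42 + 1/30) = 0.239. For g = 1 and r = 0.4 the shift is 0.4/1.732 = 0.231, or 0.231/0.239 = 0.97 standard errors. A two-sided 5% normal test then rejects with probability of about Φ(0.97 − 1.96) + Φ(−0.97 − 1.96) = 16%.

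**Step 2: simulation.** There were 8,000 runs per cell, 42 against 30, with ages beta-distributed on 3–9 years. The unadjusted Mann–Whitney test was compared with a regression of the feature's ranks on group and age. The Monte Carlo standard error at 5% is √(0.05 × 0.95/8000) = 0.24 percentage points.

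False-positive rate per feature, unadjusted Mann–Whitney:

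| Mean age gap | r = 0.2 | r = 0.3 | r = 0.4 | r = 0.5 |
|---|---|---|---|---|
| 0 | 5.0% | 4.6% | 4.7% | 4.4% |
| 0.5 year | 4.9% | 6.5% | 7.7% | 8.7% |
| 1 year | 7.5% | 10.6% | 15.2% | 21.9% |

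The 15.2% at 1 year and r = 0.4 agrees with the 16% found by hand. With age in the model, the rate was about 5% in every cell (4.7% to 5.6%). Sex was not simulated.

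**Step 3: how likely such gaps are.** If both cohorts came from the same uniform age distribution, the standard error of the difference in mean age would be 1.732 × 0.239 = 0.41 years. An observed gap above 0.5 year would arise by chance in about 23% of samples (0.5/0.414 = 1.21 standard errors). A gap above 1 year would arise in about 1.6% (1/0.414 = 2.42 standard errors). Chance gaps of this kind do not inflate the error rate on average: the zero-gap row is the rate over such samples, and it stays near 5%. The lower rows therefore need a real difference in the ages recruited. The stated criteria allow one, but nothing in the documents shows that it will occur.

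**The case against.** The strongest reply has four parts.

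- **The plan intends similar ages.** The abstract says so, and section 2.1 repeats it loosely. This stands, and it makes large gaps less likely. But the only mechanism stated for age is a roughly equal range, which does not control the distribution.
- **The analysis plan may adjust.** Section 2.6 is one condensed paragraph: it names tests for groups in general and no test for beta-diversity. Covariates could be set in a statistical analysis plan that is not shown. This limits the point to what the article states, namely covariate-free tests and an admission about age. If a fuller plan does adjust, the article should agree with it.
- **The limitation is disclosed.** It is, but disclosure does not remove the bias, and here the data needed to reduce it are already being collected.
- **The size is assumed.** This also stands. With no age gap the unadjusted test keeps its level, and at 0.5 year the inflation is modest.

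A reader might also infer that the whole search for ASD markers is compromised, because the Introduction hopes to "identify the unique bacterial and metabolic markers of ASD". The text does not support that. The Introduction ties this search to correlating symptom-scale changes with flora and metabolites, and the Discussion speaks of bacteria and metabolites linked to improved symptoms. These are analyses within Cohort 1, using Spearman's test. Nor does the Discussion say that age will be ignored altogether: it says not fully considered, and it does not mention sex, which has its own recruitment criterion.

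**Conclusion.** The point holds for one secondary comparison: the flora of ASD children at baseline against healthy children, with the parallel metabolite comparison. It is not randomised, its balance on age and sex is only roughly controlled, and the only between-group tests named cannot adjust for either. The bias is conditional. It appears only if the cohorts differ in age (or sex) and the feature depends on that factor. Under the assumptions above, the false-positive rate per feature is about 5% with no gap, 5–9% at 0.5 year and 8–22% at 1 year; age adjustment holds it near 5%. These figures illustrate the mechanism and do not predict what this trial will find. The primary CARS endpoint, the randomised comparison of FMT with placebo, and the symptom correlations within Cohort 1 are not affected. The change is still worth making, because the covariates are recorded and the article itself names age as a factor.

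**What to change.** For ASD at baseline against healthy children only, make age- and sex-adjusted models primary:

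- linear or rank-based regression on group, age and sex for alpha-diversity and for each taxon and metabolite;
- PERMANOVA with age and sex in the model for beta-diversity.

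Keep the unadjusted rank tests as sensitivity analyses, and reword the Discussion limitation to say that age and sex are adjusted for in this comparison while other factors, such as living habits, are not.

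The cost is analysis code and about two degrees of freedom from 72 children, with no new data. Recruiting healthy children by age band and sex to mirror Cohort 1 would be an optional addition; it would carry its own recruitment cost, and the adjusted analysis does not depend on it.
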